# The effects of phytosomal curcumin supplementation on clinical symptoms, and inflammatory and oxidative stress biomarkers in patients with migraine: A protocol for a randomized double-blind placebo-controlled trial

**DOI:** 10.22038/AJP.2022.21242

**Published:** 2023

**Keywords:** Curcumin, Phytosomal curcumin, Migraine, Inflammation, Headache

## Abstract

**Objective::**

Migraine is one of the most common diseases. Curcumin with anti-oxidative and anti-neuroinflammatory properties might have beneficial effects in migraine patients. This study will be conducted to evaluate the effects of a phytosomal preparation of curcumin on clinical signs, oxidative stress, and inflammatory parameters in patients with migraine.

**Materials and Methods::**

This is a randomized, double-blind, placebo-controlled, clinical trial in which, 60 patients with migraine will be assigned to receive a daily dose of 250 mg of phytosomal curcumin for 8 weeks (intervention group) or 250 mg maltodextrin as a placebo for the same duration (control group). Before and after the study, frequency, duration, and severity of the attacks, quality of life and sleep, mood status, high-sensitivity C-reactive protein (hs-CRP), Nitric Oxide (NO), and oxidative stress factors will be measured.

**Conclusion::**

It seems that phytosomal formulation of curcumin (a solid dispersion preparation of curcumin with phosphatidylserine) with high bioavailability, can cross the blood-brain barrier (BBB) and result in decreased neuroinflammation, oxidative stress, and neurotoxicity. This way, phytosomal curcumin might lead to reduction of headaches and other complications of migraine and increase the quality of life of patients with migraine.

## Introduction

Migraine as a chronic neurovascular disorder is one of the most common diseases and is considered a primary cause of disability (Agosti, 2018 ▶). It is estimated that the prevalence of migraine is about 12-14% globally and it is more prevalent in women and 35-45 year old individuals (Economics, 2018 ▶; Lipton et al., 2007 ▶). Based on Global Burden of Diseases, Injuries, and Risk Factors (GBD) studies, in 2016, about three billion people suffered from migraine or tension-type headaches. On the other hand, it has been shown that the disability weight of migraine is much higher than tension-type headache, as migraine caused 45.1 million years of life lived with disability (YLDs) while tension-type headache caused only 7.2 million YLDs. Women between ages 15 and 49 years were categorized as the most important age group with migraine headaches (Stovner et al., 2018 ▶). Although it was recently reported that the prevalence of migraine is lower in Asian countries than European countries, North America and Australia (Karimi et al., 2020 ▶), the prevalence of this disease is about 14% in Iran, which is higher than its global range (Farhadi et al., 2016 ▶).

Moderate or severe pain has occurred in about 90% of the migraineurs, and during headache attacks, the ability to function is reduced in about 75% of patients, and others (25%) need bed rest during the attacks (Lipton et al., 2007 ▶). Migraine attacks negatively affect the life quality, and the productivity in both private and social life (Lantéri-Minet et al., 2011 ▶; Farhadi et al., 2016 ▶). It was also revealed that panic and anxiety disorders are dramatically more prevalent among migraineurs compared with others (Sareen et al., 2006 ▶; Jette et al., 2008 ▶). With the increasing frequency of migraine attack episodes, the anxiety rates notably increase. Indeed, findings from a very recent systematic review showed that a major comorbidity of migraine is anxiety, with a mean of ~43% of patients who experienced comorbid symptoms (Karimi et al., 2020 ▶). Another salient fact about migraine is its large economic impact as studies in Europe showed that the average per-person costs for migraine direct and indirect costs were €1222 in a year with a total of €111 billion per year for 27 EU nations (Linde et al., 2012 ▶). In Australia, it is estimated that the cost of migraine was approximately $35.7 billion in 2018 (Economics, 2018 ▶). 

It is proposed that the central nervous system (CNS) is where migraine is originated, while some other evidence suggests that neurovascular and metabolic changes in the brain with dysfunctional intracranial and extracranial blood vessels trigger migraine (Gerring et al., 2018 ▶). Nevertheless, the etiology and pathophysiology of migraine is too complex and not fully understood, and to date, the main cause of migraine attack is unclear (Tajti et al., 2011 ▶). Diverse parameters have been considered migraine triggers such as stress, neuroendocrine imbalances, hormones, oxidative stress, inflammation, too much or too little sleeping, and unhealthy diet and allergenic foods (Hauge et al., 2010 ▶; Finocchi and Sivori, 2012 ▶; Theeler et al., 2010 ▶; Kursun et al., 2021 ▶; Borkum, 2016 ▶). Recent evidence suggests that inflammation through activation of nociceptive sensory neurons has a crucial role in the pathology of pain initiation as well as pain persistence (Sommer and Kress, 2004 ▶). In this regard, an accumulating body of evidence declared that stress, oxidative, and inflammation play a significant role in migraine attacks (Borkum, 2016 ▶; Kursun et al., 2021 ▶; Edvinsson et al., 2019 ▶). The immune system through production of inflammatory factors, namely, cytokines, including tumor necrosis factor (TNF), interleukin (IL) 1 (IL-1), and adiponectin increase headache (Kursun et al., 2021 ▶). Injection of TNF induces headache, while TNF antibody decreases pain in humans (Bruno et al., 2007 ▶). Pro- and anti-inflammatory cytokines increase in the plasma during migraine attacks. Higher level of TNF-α and IL-6 was observed in migraine patients compared with healthy individuals during and between attacks (Yilmaz et al., 2010 ▶). 

Although migraine is becoming one major health issue all around the world, to date, there is no exclusive and comprehensive treatment approach, medical care, or pharmacological agents for its prevention or treatment (Katsarava et al., 2018 ▶). 

Up to the present time, pharmacological care for the treatment of migraine headaches includes triptans, ergot derivatives, and analgesics (NSAIDs). Some other oral drug, originally produced for treatment of epilepsy, depression or high blood pressure, are also applied for the prevention of migraine attacks. Finally, botulinum toxin A injection was approved in 2013 as a preventive therapy in migraine patients who are non-responders to oral preventive medications. Considering several adverse and unfavorable effects as well as the high costs of these medications (D'Amico and Tepper, 2008 ▶; Mayans and Walling, 2018 ▶), and with regard to the facts that patients with severe and/or frequent migraine need long-term preventive medications, several non-pharmacological methods, including nutraceuticals, herbal medicine, behavioral techniques and acupuncture have attracted significant attention to manage migraine in clinical settings (Puledda and Shields, 2018 ▶). Indeed, today, monotherapy remedy is replaced by multiple therapies according to the multiplicity of targets (Mythri and Bharath, 2012). To achieve this purpose, intense investigations are being conducted to assess the combination of modern/conventional pharmacological therapies with medicinal plants, including herbal bioactive compounds and phytochemicals (Kumar, 2006 ▶; Sparreboom et al., 2004 ▶). 

Herbal medicine as a safe, inexpensive, available, and accessible therapy approach is becoming one of the most attractive field of study to prevent and treat neurological disorders such as migraine. Medicinal plants can be considered a complementary and alternative method to prevent and treat migraine since these are an acceptable and favorable therapeutic approach for most of the patients.

Curcumin is a yellow polyphenolic pigment and the principal polyphenol and a key bioactive compound of turmeric, which has been used in traditional medicine for thousands of years. A wide range of beneficial properties are attributed to curcumin (Hewlings and Kalman, 2017 ▶; Bagherniya et al., 2018 ▶; Farhood et al., 2019 ▶; Mortezaee et al., 2019 ▶; Panahi et al., 2014 ▶; Parsamanesh et al., 2018 ▶; Shakeri et al., 2019 ▶; Javandoost et al., 2018 ▶; Kheiripour et al., 2021 ▶; Ghasemi et al., 2022 ▶; Atabaki et al., 2022 ▶). Its neuroprotective properties, as well as its anti-neuroinflammatory effects make it a focus of attraction in the area of neuroscience. Neuroprotective effects of curcumin are attributed to its antioxidant, anti-inflammatory, and anti-protein-aggregate activities (Cole et al., 2003 ▶). Specifically, several animal studies indicated the promising effects of curcumin on neurodegenerative disorders (Park and Kim, 2002 ▶; Zhang et al., 2011 ▶; Frautschy et al., 2001 ▶; Thiyagarajan and Sharma, 2004 ▶). It seems that curcumin might have beneficial effects on migraine signs and symptoms as a very recent systematic review showed that curcumin supplementation had positive effects on the reduction of inflammation and stress oxidative and decreasing the frequency, severity, and duration of migraine attacks (Mohseni et al., 2021 ▶). However, as in this review mentioned, factors that decrease the efficacy of curcumin in the clinical setting are its poor absorption and low bioavailability. It is recommended to use other forms of curcumin such as nano-curcumin, curcumin-piperine, and phytosomal curcumin to overcome the above limitations of the curcumin usage (Mohseni et al., 2021 ▶). 

Curcumin bioavailability increases using the phytosomal formulation of curcumin (a complex of curcumin with phosphatidylserine). Physicochemical properties including amphiphilic nature causes dispersion in both hydrophilic and lipophilic media, which appear with the abundance of phospholipids in phytosomes (Mirzaei et al., 2017 ▶). On the other hand, phosphatidylserine exists in abundant amounts in myelin in the healthy human brain, and its amount in the grey matter increases two times from birth to 80 years of age (Glade and Smith, 2015 ▶). To keep the health of nerve cell membranes and myelin, phosphatidylserine is needed. The absorption efficacy of oral phosphatidylserine is high and it can cross the blood-brain barrier (BBB) subsequent to its absorption into the bloodstream (Glade and Smith, 2015 ▶). 

Altogether, it seems that phytosomal curcumin with high levels of absorption which might cross BBB, could be useful in migraine patients as a novel treatment agent. Different forms of curcumin such as nano-curcumin were previously assessed in migraine patients, and produced promising results in terms of migraine clinical symptoms and also in reduction of inflammation and oxidative stress and the other related factors in these patients (Sedighiyan et al., 2022 ▶; Rezaie et al., 2021 ▶; Abdolahi et al., 2021 ▶; Parohan et al., 2021 ▶). However, to the best of our knowledge, no study evaluated the effects of phytosomal curcumin on migraine patients. Thus, this study will be conducted to evaluate the effects of phytosomal curcumin on clinical outcomes and stress oxidative and inflammatory parameters in migraine patients. 

## Materials and Methods

This protocol was written based on CONSORT SPIRIT 2013 guidelines (Chan et al. 2013 ▶). This study is a parallel double-blind randomized clinical controlled placebo trial in which, a total of 60 migraine patients will be included. The trial design is illustrated in Figure 1.  Patients will be chosen from neurology clinics (Imam Moosa, Sadr, and Khorshid) affiliated to Isfahan University of Medical Sciences from July 2022. To include in the study, subjects will be screened by an experienced neurologist according to our inclusion and exclusion criteria. 

**Eligibility criteria**

Participants will be included in the study according to the following criteria: 

**Inclusion criteria**

a) migraine without aura, migraine will be diagnosed by an expert neurologist (FK) based on ICDH-3 criteria (Munoz-Ceron et al., 2019 ▶) b) history of migraine for at least one year, c) age between 20–60 years old, d) following routine and steady treatment for the management of migraine headaches for at least 4 weeks before of the study, and e) willingness to participate in the study and fulfil the written consent form

**Exclusion criteria**

a) Having other types of headache such as tension-type headache, cluster headache, medication overuse headache, trigeminal autonomic cephalalgias, or headache due to menstrual, b) Pregnancy or lactation, c) history of chronic diseases (i.e. diabetes, high blood pressure, gastrointestinal (GI) disorders like Crohn’s and ulcerative colitis, cancer, or liver, kidney, or thyroid disease), d) any changes in the pharmacological treatment such as type and dose of the drugs, e) Migraine with aura, f) Other neurological disorders, g) taking antioxidant supplements for at least 3 months before the study, h) Following a special diet for at least 3 months before the study, i) Having allergies to herbal medicine, particularly to turmeric and ginger, j) Smoking and alcohol consumption, or k) Individuals with poor compliance to the intervention (less than 80%).

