**Randomization **

Eligible patients who fulfill the inclusion criteria will be enrolled in the study. At first, the included patients will be randomized (1:1) into intervention or control groups. We will use a permutated block randomization approach to stratify subjects according to migraine severity with a block size of 4. We will use a table of random numbers to perform random assignment. In addition, patients will be enrolled and assigned into intervention and control groups by a well-trained nutritionist. Allocation concealment will be performed by sequentially numbered containers. 

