**Intervention**

Patients in the intervention group will receive one capsule/day containing 250 mg phytosomal curcumin (250 mg containing 20% curcuminoids and 20% phosphatidylserine; Indena SpA, Milan, Italy), for 8 weeks. On the other hand, patients in the control group will receive one capsule/day containing 250 mg maltodextrin, for the same duration. Participants will be asked to take each capsule one hour after breakfast. Moreover, we will instruct the patients in both groups to follow their usual diet and physical activity as well as their medication therapy exactly as their neurologist prescribed. 

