**Assessment of mood status (stress, anxiety, and depression)**

A modified DASS-21 questionnaire for Iran will be used to assess mood at the beginning and end of this study (Samani and Joukar, 2007). The DASS-21 subscales consist of 21 questions, seven questions for stress, seven for anxiety, and seven for depression. Each question is scored from zero (does not apply to me at all) to 3 (absolutely applies to me). The subscales should be doubled, then the severity of the symptoms can be determined as shown in Table 2 (Lovibond and Lovibond, 1995 ▶).

**Table 1 T1:** Timeline and applied tests

**Activity**	Time (Week)								
	0	1	2	3	4	5	6	7	8
**Enrollment**	*								
Eligibility screening Informed consent Randomization Allocation	*								
	*								
	*								
	*								
Sociodemographic	*								
Intervention		*	*	*	*	*	*	*	*
Placebo (maltodextrin, 250 mg)		*	*	*	*	*	*	*	*
Intervention (250 mg phytosomal curcumin)		*	*	*	*	*	*	*	*
Compliance and side effects		*	*	*	*	*	*	*	*
Laboratory tests	*								*
VAS	*								*
HIT-6	*								*
MSQ	*								*
DASS-21	*								*
Food record	*								*
Physical activity recall	*								*

**Table 2 T2:** Intensity of each subscale for assessment of mood status

**Severity **	**Depression**	**Anxiety**	**Stress**
**Normal**	0-9	0-7	0-14
**Mild**	10-13	8-9	15-18
**Medium**	14-20	10-14	19-25
**Intense**	21-27	15-19	26-33
**Very intense**	+28	+20	+34

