**Statistical methods**

The analysis will eventually be performed in the form of Intention-To-Treat (ITT) and Per-Protocol (PP) using the SPSS software, version 22 (SPSS Inc, Chicago, IL, USA). Quantitative data will be reported as mean±standard deviation (SD), and qualitative data will be presented as frequency and percent. Normality of the data will be assessed using Kolmogorov-Smirnov test. Paired t-test will be applied to evaluate the differences in each group before and after intervention. Independent T will be used to show the baseline and endpoint differences between the two groups. We will apply analysis of covariance (ANCOVA) to show differences between two treatment groups after adjusting for confounding variables. P-value less than 0.05 will be considered statistically significant. 

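### Exclusion criterion k (compliance below 80%) can act only after randomisation and, applied as written, conflicts with the promised ITT analysis; criterion d is ambiguous on timing

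*Protocol article*

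**What the plan says.** All of this is in the Materials and Methods of the Protocol article.

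- **Exclusion criteria, item k:** "Individuals with poor compliance to the intervention (less than 80"%).
- **Exclusion criteria, item d:** "any changes in the pharmacological treatment such as type and dose of the drugs". No period is attached. Items g and h in the same list do have one; g, for example, reads "taking antioxidant supplements for at least 3 months before the study".
- **Inclusion criteria, item d:** "following routine and steady treatment for the management of migraine headaches for at least 4 weeks before of the study".
- **Randomization:** "At first, the included patients will be randomized (1:1) into intervention or control groups". No run-in precedes this step.
- **Table 1 (timeline):** randomisation and allocation are marked at week 0. The row "Compliance and side effects" is marked at weeks 1 to 8 and not at week 0. Laboratory tests and questionnaires are scheduled at weeks 0 and 8.
- **Intervention:** during treatment, patients in both groups are told to keep to "their medication therapy exactly as their neurologist prescribed".
- **Statistical methods:** "The analysis will eventually be performed in the form of Intention-To-Treat (ITT) and Per-Protocol (PP"). Neither set is tied to the 80% threshold.

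**The concern.** An eligibility criterion decides who may be randomised. Compliance with the study capsule does not exist until a patient has been randomised and has started taking it. Placed among the exclusion criteria, item k therefore tells site staff to take out patients who are already in the trial.

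An ITT analysis rests on the opposite principle: patients stay in the comparison as randomised, whatever they did afterwards. If non-compliers are excluded under k, the groups compared are no longer those that randomisation formed. Non-compliance may follow poor response or side effects, and either may differ between arms. Blinding does not prevent this. If exclusion also meant that no week-8 measurement was taken, no later analysis plan could restore the data.

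Item d raises the same question less sharply, because a drug change may also be a response to how the headaches are going.

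**Working it through.** **Timing of item k**

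1. Randomisation is at week 0 (Table 1).
2. Compliance is recorded in weeks 1 to 8 (Table 1).
3. No run-in is described (Randomization section and Table 1).
4. So nobody can meet item k before randomisation, and everyone whom it excludes is a randomised patient.
5. Statistical methods promises ITT as well as per-protocol. A set from which k has removed patients is not the set as randomised; it has moved towards the per-protocol set.

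**Timing of item d**

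- For a reading that includes the treatment period: items g and h name a period before the study and d does not; stability before the study is already inclusion criterion d.
- For a reading limited to screening: the list repeats another inclusion criterion in negative form (exclusion e, aura, mirrors inclusion a), so overlap with inclusion d proves little.
- A further tension: a patient whose neurologist changes a prescription during the trial complies with the Intervention section and, on the wider reading, meets exclusion d.

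The text does not settle d.

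**Selection bias**

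Let a share p of an arm be removed, and let those removed average g SD worse than those kept. The mean of those kept then lies p × g better than the mean of the whole arm. The bias in the comparison, in favour of curcumin, is

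p(curcumin) × g(curcumin) − p(placebo) × g(placebo).

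The document gives none of these four quantities, so neither size nor sign can be computed. If more of the worst placebo patients were removed, the result would be negative, that is, against curcumin.

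**What a full ITT analysis costs in power**

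Inputs from the section on power and sample size: alpha 0.05, power 80%, 23 per group, raised to 30 for dropout. The difference, the SD and the dropout rate are not given, so 23 and 30 can only be solved backwards.

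- Implied difference (two-sided test assumed, normal approximation): √(2/23) × (1.960 + 0.842) = 0.826 SD. A calculated size of 23 fits differences from 0.83 to 0.84 SD; a one-sided test would imply about 0.73.
- Implied dropout allowance: 1 − 23/30 = 23.3%.

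Assume that a share c of curcumin patients does not comply and gets no effect, that the SD is unchanged, and that all 30 per arm are measured. The ITT difference is then 0.826 × (1 − c). Power is Φ(0.826 × (1 − c) × √(30/2) − 1.960). The number per arm for 80% power is 23/(1 − c)², rounded up.

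| c | ITT difference (SD) | ITT power, 30 per arm | Per arm for 80% | If non-compliers are removed: left per arm, power |
|---|---|---|---|---|
| 10% | 0.74 | 82% | 29 | 27, 86% |
| 20% | 0.66 | 73% | 36 | 24, 82% |
| 23.3% | 0.63 | 69% | 40 | 23, 80% |
| 30% | 0.58 | 61% | 47 | 21, 76% |

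The last column supposes that the same share is removed from both arms and that removal is unrelated to outcome. It shows what is given up, and is no argument for removing patients.

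**The case against.** The strongest reply is that item k is simply a per-protocol definition in the wrong list. Promising both analyses makes sense only if some randomised patients are expected to fall outside the per-protocol set, and an 80% threshold is a usual way to define it. This is plausible. A reader might go further than the text and infer that non-compliers lose their week-8 visit, or that the ITT and per-protocol sets become identical. The document says neither: it does not state that follow-up stops or that these patients leave the ITT analysis. What stands is that k, where it is printed, excludes them, and that nothing in Statistical methods undoes this.

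Four other inferences are tempting and not supported:

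- **That item d certainly removes patients for drug changes during treatment.** The missing time window favours that reading, but a screening-only reading remains open.
- **That 7 of 30 per arm is a budget for compliance exclusions.** The article presents the increase from 23 to 30 as an allowance for dropout.
- **That poor tolerability will cause unequal loss between arms.** The Safety consideration section mentions nausea and diarrhoea in connection with 8,000 mg/day and expects no considerable adverse effects from the trial's capsules. Unequal loss is possible but not shown.
- **That not naming a main analysis is itself a fault.** A condensed article may leave that to the full protocol or analysis plan.

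None of this rescues k as an eligibility criterion. An analysis plan can define sets, but it cannot supply outcomes that were not collected.

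**Conclusion.** The point holds for item k, and it rests on timing alone: the criterion can be met only after randomisation, and applying it as an exclusion is incompatible with ITT. This is a rule that the article states, not a detail left out, and it should be corrected. For item d the conclusion is weaker: its timing is ambiguous and must be reconciled with inclusion criterion d and with the medication instruction under Intervention.

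The possible bias has no derivable size or direction. The power figures are illustrations. They rest on a two-sided test, on the difference of about 0.83 SD solved back from 23 per group, and on no effect in non-compliers. On those assumptions 30 per arm keeps 80% power at 10% non-compliance but not at 20%.

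**What to change.** - Remove item k from the exclusion criteria and use the 80% threshold only to define the per-protocol set.
- State that item d, as an eligibility criterion, applies only before randomisation, consistent with inclusion criterion d, and reconcile its wording with the Intervention section.
- State that all randomised patients are followed to the scheduled week-8 assessment and analysed as randomised in the ITT analysis, whatever their compliance or later drug changes.

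The cost is protocol wording, the effort of obtaining week-8 data from patients who stop capsules (the assessment is already in Table 1), and a diluted ITT effect. The sponsor should check whether 30 per arm is still enough at the non-compliance it expects; on the assumptions above, 80% power would need about 36 per arm at 20% and 40 at 23.3%.
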